### Data collection

A research assistant (RA) is responsible for recruitment at each of the study sites. The list of patients to be seen each day is pre-screened to identify those ineligible. Eligible patients are invited to meet with the RA who explains the study. In an observational study, it is essential to establish the extent to which the sample is representative of the target population, by collecting key information about those who decline participation, in order to understand the potential for selection bias. Therefore, those unwilling to enter the study are asked to provide a reason and respond to two questions about cognitive concerns, both of which are items from the B-CAM, and indicate age and whether they are currently working.

Those who agree to enter the study provide written, informed consent (see below). Participants next respond to the questionnaire measures directly on a clinic-based computer, guided and overseen by the study research assistant as needed, and then, if they wish, complete them at home. Data collection uses the Dacima Clinical Suite version 3 (Dacima Software Inc.) electronic data capture (EDC) software platform. The EDC platform allows data to be entered into a secure, web-based database that complies with regulatory requirement (FDA 21 CFR Part 11) through any browser. The software includes a complete audit trail, subject and data entry status tracking, real-time data validation checks, dashboards/reporting and data extraction functionalities. Data capture takes about 90 min at the first visit, and 60 min at follow-up. Site RAs assist with the administration of the B-CAM, ensure questionnaire measures are completed, and enter demographic and medical information, including standard of care blood test results abstracted from computerized clinical databases, anthropomorphic measures, patient report and chart review into the web-based data management system. The B-CAM is carried out on a separate Internet-based platform (Inquisit, Millisecond Software), and merged with the other data for further analysis.

### Statistical methods and sample size

#### Aim 1: To estimate the extent to which HIV-related clinical factors and patient-centered outcomes relevant to brain health and its consequences inter-relate and evolve over time and to explore the mechanisms underpinning longitudinal change in brain health

The analysis will estimate the complex relationships between cognitive ability, other indicators of brain health, other symptoms, such as pain, functions in everyday life, health-perception, and quality of life (QOL). We will trace the connections between biological variables, objective measures of cognition, and the constructs that really matter to patients (such as perceived health, which predicts longevity [34, 35], and QOL--the reasons for living), using the Wilson-Cleary model. The advantage of this approach is that the antecedents, correlates, and consequences of brain health can be fully described, leading to a better understanding of how to optimize function, perceived health, and QOL in the presence of lower cognitive ability.

Structural Equation Modeling (SEM), one of a family of related, sophisticated, multivariate statistical procedures, will be used to test how well the Wilson-Cleary theoretical model conforms to the data. SEM consists of two basic elements: a measurement model, analyzed by factor analysis, and a structural model, using path analysis. SEM uses latent variables to represent the constructs of interest, recognizing that complex constructs are not adequately represented by any one single measure, and thus the commonality between related measures is a better representation [36]. This method will permit the direct and indirect effects of cognitive deficits to be situated within the broader context of HIV morbidity, co-morbidities and life impact of HIV infection.

Sample size for SEM is large: optimally 15 to 20 people per parameter estimated. The number of parameters estimated in a complex model can be substantial (approximately three per included latent variable) therefore sample sizes in the range of 400 to 600 are needed for the Wilson-Cleary model. Given the focus on cognition, it will be informative to identify if the structure and relationships between and among variables differ in the presence of lower cognitive ability. As we are expecting about 40 % to have some cognitive deficit, a sample size of 900 would yield about 360 persons for an SEM model. The model will also be fit longitudinally, providing the opportunity to understand how changes in key constructs affect brain health and function over time.

To address heterogeneity of the HIV population in terms of evolution of cognitive ability over time, and co-evolution of cognitive ability with antecedent variables, correlates and consequences, a form of latent trajectory analysis (group-based trajectory analysis; GBTA) [37] will be used. This analysis is optimized with four or more time points. This approach has been used to characterize evolution of cognitive impairment over time in an elderly population [38, 39], and apathy in a stroke population [38]^5^. GBTA assumes the population is made up a mix of people with different longitudinal trajectories and uses a semi-parametric approach to group like with like. The optimal number and shape of trajectories is determined by theory, Bayesian Information Criteria (BIC), magnitude of the average posterior probability of group assignment (with ≥0.70 recommended), and closeness of the theoretical and assigned proportions of people to trajectories [37].

The sample sizes projected for this study should yield up to 5 to 7 distinct trajectories [40], providing a detailed view of the heterogeneity of longitudinal change and of factors contributing to trajectory of change. Additional multivariate approaches may be warranted, such as mixed models, to assess the impact of key variables on longitudinal change in brain health.

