### Measurement strategy: the brain health platform

We will apply a theory-based measurement framework, the Wilson-Cleary outcome model, to structure this portion of the study (Fig. 2). This model is widely used to assess the life impact of medical conditions. The model comprehensively considers the relationship between characteristics of the individual, and of their environment, as they relate to a continuum from biological variables, to symptoms, to functional status and quality of life [26]. There have been three studies using the Wilson-Cleary model in HIV, with a restricted set of variables, and none including cognitive constructs [26–28]. Figure 2 and Table 1 present the constructs measured in the current study in all patients within the Wilson-Cleary framework. We have situated the brain health measures within the ‘symptom’ and ‘function’ rubrics of this model. Information on the key constructs is collected through chart review, face-to-face interviewing and direct testing, and through questionnaires. All questionnaires are brief and well known in the health literature, and widely tested in various populations, permitting comparisons across health conditions. To assure wide application to the broader clinical context, we selected measures that are in the public domain and available in English and French. The platform will serve as a sampling frame for a series of trials targeting brain health in selected sub-groups.

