**Fig. 2 Fig2:**
[figure not shown]
Wilson-Cleary outcome model. Characteristics of the individual include motivation, symptom amplification; characteristics of the environment include psychological and social supports

**Table 1 Tab1:** Constructs to be measured within the structure of the Wilson-Cleary framework

Characteristics of the individual				
Age, sex, self-declared race, height, weight, education, work status, occupation, living situation, cognitive reserve indicators, coping, smoking, alcohol, drug use, healthy eating behaviour				
Biological and physiological variables	Symptom status	Functional status	Health perception	Quality of life (QOL)
Nadir CD4+, current immunological markers, current viral load, peak viral load, current ARV treatment, duration of HIV infection; Co-morbidities: diabetes, cardiovascular disease, hypercholesterolemia, hepatitis B & C, vitamin B12, thyroid-stimulation hormone (TSH), others Medications	Physical Symptoms: vitality, pain, sleep quality, HIV related signs and symptoms	Measured and self-reported cognitive deficits; cognitive ability; self-efficacy	General health perception; health utility	Personalized QOL; HIV-specific QOL
	Emotional symptoms: anxiety, stress, depression, apathy	Physical activity; physical function; self-efficacy for managing HIV health challenges		
		Role participation: work status, work quality, nature and frequency of leisure activities, life space mobility		
Social and psychological supports				
Social support, self-management priorities				

*ARV* anti-retroviral

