#### Aim 2. To contribute evidence for the validity of a brief brain health assessment approach (B-CAM)

The strength of the relationship between the results of the reference standard cognitive assessment and the B-CAM will be tested using rank correlation and sensitivity and specificity. To formally estimate the sensitivity and specificity of B-CAM, we will use the classical method of Begg and Greens [41], which assesses diagnostic tests when there are different verification probabilities. Because the new measure, B-CAM, is mapped to a standard normal distribution (on a logit scale), it is possible to use the distribution to identify a cut-point for further testing. Validation will take place on the first 500 consecutive persons enrolled. The sample size for this estimation is based on the formula provided by Begg and Greens for sensitivity, specificity and corresponding 95 % confidence intervals (CI). Assuming that approximately 40 % of people will score in a range indicative of cognitive deficit on B-CAM, we will recruit 100 % of all those with B-CAM evidence of deficit (500 * 0.4 = 200) plus 20 % of the remainder (300 * 0.2 = 60). With this verification strategy, and under the assumptions above, the estimated sensitivity is 0.86 (95 % CI: 0.73 to 0.93). The corresponding values for specificity are 0.93 (95 % CI: 0.89 to 0.96). We will also estimate the effect of covariate status (age, co-infection with hepatitis C, history of drug use, recent immigrant, or low education) on sensitivity and specificity.

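### Fitting the Aim 1 SEM only in people with cognitive deficit selects on a variable inside the model, which weakens paths into cognition even if nothing truly differs

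*Protocol article*

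**What the plan says.** In the protocol article, the Aim 1 part of the statistical methods uses SEM to test the Wilson-Cleary model. It then adds that "it will be informative to identify if the structure and relationships between and among variables differ in the presence of lower cognitive ability". The next sentence sizes this: "As we are expecting about 40 % to have some cognitive deficit", so "a sample size of 900 would yield about 360 persons for an SEM model". The natural reading is a separate SEM fitted in the cognitive-deficit subgroup.

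The same article puts cognition inside that model. The measurement strategy section describes "a continuum from biological variables, to symptoms, to functional status and quality of life" and locates the brain health measures at the symptom and function levels. Table 1 lists "Measured and self-reported cognitive deficits; cognitive ability; self-efficacy" under functional status, downstream of the biological and symptom columns. Aim 1 promises that "the antecedents, correlates, and consequences of brain health can be fully described".

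The Aim 1 text does not define deficit and does not name the comparator for the subgroup fit. Aim 2 uses the same percentage for the B-CAM: "Assuming that approximately 40 % of people will score in a range indicative of cognitive deficit on B-CAM".

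**The concern.** A variable with modelled causes is endogenous. Keeping only people at its low end truncates it, with three consequences when the model is refitted in that group:

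- Paths from biological and symptom variables into cognition shrink, and so do indirect effects that run through cognition.
- Causes that are independent in the cohort become correlated. The correlation is negative if both act on cognition in the same direction and positive if they act in opposite directions.
- Standardised paths leaving cognition shrink because its variance is smaller. Unstandardised ones do not.

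The subgroup fit can therefore suggest that contributors matter less, or are related differently, at lower cognitive ability purely because of how the group was formed. That would be a wrong answer to the question the article poses. The error is systematic, so a larger subgroup would not remove it.

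**Working it through.** **The article's figure.** 900 × 0.40 = 360. It is reproduced exactly; the issue is how the group is formed.

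**Inputs from the article.** Cohort 900; selected share 40%; cognition downstream of biological variables and symptoms.

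**Assumptions (not in the article).** Normal variables with variance 1 in the cohort; two independent causes, each with the same path *b* into cognition, *b* from 0.2 to 0.5; a path of 0.5 from cognition to a later outcome; identical structure in everyone. The selection measure correlates ρ with modelled cognition: ρ² = 1 (selection on cognition itself), ρ² = 0.8 (reliability 0.8), or ρ = 0.7 (ρ² = 0.49).

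**Step 1: variance left after keeping the lowest 40%.** The cut is c = −0.253. With λ = φ(c)/0.40 = 0.966, the retained variance is V = 1 − cλ − λ² = 1 + 0.245 − 0.933 = 0.312. For the upper 60% it is 0.422.

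**Step 2: carry the selection through the model (Pearson-Lawley formula).** With k = (1 − V)ρ²:

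- low-group path = b(1 − k) / (1 − 2kb²)
- induced correlation between the causes = −kb² / (1 − kb²)

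Example, ρ² = 1 and b = 0.4: k = 0.688; path = 0.4 × 0.312 / (1 − 2 × 0.688 × 0.16) = 0.125/0.780 = 0.16; correlation = −0.110/0.890 = −0.12.

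| True path | Low-group path, ρ² = 1 | ρ² = 0.8 | ρ = 0.7 | Induced correlation, ρ² = 1 | ρ² = 0.8 | ρ = 0.7 |
|---|---|---|---|---|---|---|
| 0.2 | 0.07 | 0.09 | 0.14 | −0.03 | −0.02 | −0.01 |
| 0.3 | 0.11 | 0.15 | 0.21 | −0.07 | −0.05 | −0.03 |
| 0.4 | 0.16 | 0.22 | 0.30 | −0.12 | −0.10 | −0.06 |
| 0.5 | 0.24 | 0.31 | 0.40 | −0.21 | −0.16 | −0.09 |

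For ρ = 0.7, k = 0.688 × 0.49 = 0.337. The correlations are shown for causes acting in the same direction; the sign reverses if they oppose.

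**Step 3: indirect effect, true path 0.4.** In the cohort it is 0.40 × 0.50 = 0.20. In the low group it is 0.16 × 0.50 = 0.08 (ρ² = 1) or 0.30 × 0.50 = 0.15 (ρ = 0.7).

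**Step 4: paths leaving cognition.** The unstandardised path stays at 0.50. The standardised one falls from 0.50 to 0.31 (ρ² = 1) or 0.36 (ρ² = 0.8).

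**Step 5: how often a false difference is declared.** This was simulated with 900 people, 360 of them in the low group, 4,000 runs and selection on cognition itself, using nominal 5% tests of path equality:

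- low group against the full-cohort fit (treated as independent): 92% at b = 0.2 and 100% at 0.3 to 0.5
- low group against the other 60%: 9%, 15%, 23% and 35% at b = 0.2, 0.3, 0.4 and 0.5
- induced correlation significant in the low group: 9%, 23%, 66% and 98%

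The rates against the other 60% are lower because that group is truncated too: at b = 0.4 its path is 0.21, against 0.16 in the low group. All these rates fall when the selection measure is noisier. Fitting all 900 recovers the true paths (means 0.199, 0.300, 0.400 and 0.500).

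**The case against.** The strongest reply is that this is one sentence in a sample-size paragraph of a condensed article, and that much of the size is inferred. Several parts of that reply stand.

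- **Definition of deficit.** Reading the cut as B-CAM is an inference from the shared 40%. The article also gives a PDQ threshold and a HAND diagnosis from the reference battery. Any definition based on cognition biases paths in the same direction, but by less if it tracks modelled cognition loosely. At a correlation of 0.5, a true path of 0.40 falls only to 0.35.
- **Path values.** None is given, so only a range can be stated. At weak paths the induced correlation is negligible.
- **Comparator.** A reader might infer that a false difference is almost certain. That holds only against the full-cohort fit with selection on, or very close to, modelled cognition. The article does not name that comparator.
- **Purpose.** Aim 1 stresses optimising function, perceived health and QOL at lower cognitive ability. Those are paths leaving cognition, and their unstandardised values survive.
- **Longitudinal fit.** A reader might also expect the low group to drift upwards by regression to the mean. The article says the model will be fitted longitudinally, but not that the low subgroup is followed alone; its trajectory analysis addresses the heterogeneity of the HIV population. That inference is not supported.

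What the reply does not remove is the subgroup fit itself. The article states it, sizes it and ties it to structure and relationships in general, which includes paths into cognition. An unseen analysis plan could add detail, but an SEM confined to these 360 people would still carry the bias.

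**Conclusion.** The concern holds, with limits. The planned subgroup SEM selects on an endogenous construct, so its paths into cognition, its indirect effects through cognition and the correlations among causes of cognition cannot be read as evidence that relationships differ at lower ability.

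Over the assumed range, the low-group path keeps about one third to one half of its true value if selection is on modelled cognition (0.07/0.2 to 0.24/0.5), and about 70% to 80% if the selection measure correlates 0.7 with it (0.14/0.2 to 0.40/0.5). The induced correlation runs from about −0.01 to −0.21 for causes acting in the same direction. With selection on cognition itself, false path differences are near certain against the full-cohort fit and occur in about 9% to 35% of studies against the other 60%.

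It would be wrong to infer that Aim 1 as a whole is compromised. The subgroup fit is an exploratory addition. The main SEM in all 900, the trajectory analysis, the Aim 2 validation and the Aim 3 trials are untouched. The point merits correction but does not threaten the study.

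**What to change.** Fit one SEM in all 900 with cognition kept continuous, which also suits the article's own view of cognitive ability as a quantity and not a category. Test whether relationships depend on cognitive level through an interaction or quadratic term in cognition, on the paths leaving it (to role participation, health perception and QOL). State that paths into cognition, and correlations among its causes, will not be interpreted from any group selected on cognition. If contributors at low ability are of interest, quantile regression of B-CAM in all 900 is an optional supplement; it does not replace the latent-variable model.

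Reword the sentence that derives 360 people for an SEM so that it describes this analysis. The cost is plan wording and a somewhat more complex model, with no new data or participants.

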### Study population

The target population is people in middle age and older, the group felt to be most at risk of both longer-term effects of HIV infection and the interaction between these and aging-related brain changes: Inclusion criteria are age ≥35, HIV+ for at least 1 year, able to communicate adequately in either French or English, and able to give written informed consent. If necessary, we will oversample patients >60 years old and women to ensure at least 100 of each are enrolled. The focus is on milder cognitive deficits, which is the area of greatest clinical uncertainty. Thus, exclusion criteria include dementia (MoCA <18) [25], or treating physician’s concern about capacity to consent, life expectancy of <3 years or other personal factor limiting the ability to participate in follow-up, non-HIV-related neurological disorder likely to affect cognition, known active CNS opportunistic infection or hepatitis C requiring Interferon-based treatment during the follow-up period, psychotic disorder, or current substance use disorder or severe substance use disorder within the past 12 months. Individuals with current or past major depressive disorder are eligible for the core project, and indeed will be the focus of one of the studies under our third aim. There are additional inclusion/exclusion criteria for individual sub-studies, described below. A brief questionnaire is used to identify characteristics of all persons approached for recruitment to determine whether non-participation introduces a selection bias into our study.

The core of the research program is the development and follow-up of a comprehensively characterized cohort of persons with HIV. The cohort is being assembled through consecutive sampling from five clinics in several large cities in Canada: Montreal, Toronto, Hamilton, and Vancouver. These clinics collectively manage thousands of patients, with diverse demographic and HIV risk profiles, most of whom are routinely followed at 3 month intervals. A total of 900 participants will be comprehensively assessed and followed longitudinally at 9 month intervals over a 3 year period (four assessments).

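### The SEM in participants with lower cognitive ability would have about 360 people, below the 400 to 600 that the same paragraph says the model needs, and the gap is not acknowledged

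*Protocol article*

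**What the plan says.** The point lies in the Aim 1 part of Statistical methods and sample size in the protocol article.

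- The rule is "optimally 15 to 20 people per parameter estimated", with the number of parameters put at "approximately three per included latent variable".
- From this the text concludes that "sample sizes in the range of 400 to 600 are needed for the Wilson-Cleary model".
- It then adds a comparison by cognitive level: "it will be informative to identify if the structure and relationships between and among variables differ in the presence of lower cognitive ability".
- The numbers for that comparison follow directly: "we are expecting about 40 % to have some cognitive deficit", so "a sample size of 900 would yield about 360 persons for an SEM model".
- The next sentence says: "The model will also be fit longitudinally".

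The text does not mention a smaller model, a lower ratio or a joint fit of both groups for the 360, and it does not remark that 360 is less than 400.

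**The concern.** The requirement and the expected yield stand a sentence or two apart, and the second does not meet the first. The 360 is offered as support for a cohort of 900, yet by the paragraph's own standard it is too few for the model just described.

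The stated question is whether the structure differs at lower cognitive ability. Answering it implies fitting the same model in that group as in the comparison, since a reduced model could not be set against the full one path by path. If the full model is fitted separately to 360 people with fewer participants per parameter than the plan calls optimal, apparent differences from the rest of the cohort may reflect unstable estimates rather than a different structure.

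**Working it through.** **Inputs, all from the Aim 1 text unless noted.** Total 900; expected share with a deficit 40%; 15 to 20 people per parameter; about 3 parameters per latent variable; stated need 400 to 600. The Background cites a prevalence of 30 to 50% for HIV-associated neurocognitive disorders.

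**1. The plan's own figure.** 900 × 0.40 = 360. This reproduces exactly.

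**2. Yield against need.**
- Lower bound: 400 − 360 = 40, and 40/400 = 10% short.
- Upper bound: 600 − 360 = 240, and 240/600 = 40% short.

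**3. What 360 supports under the stated rule.**
- At 20 per parameter: 360/20 = 18 parameters, or 18/3 = 6 latent variables.
- At 15 per parameter: 360/15 = 24 parameters, or 24/3 = 8 latent variables.

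**4. What model size the 400 to 600 implies.** The article gives no count of parameters or latent variables, so this step is inference.
- 9 latent variables: 27 parameters, needing 27 × 15 = 405 to 27 × 20 = 540.
- 10 latent variables: 30 parameters, needing 30 × 15 = 450 to 30 × 20 = 600.

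Together these span 405 to 600, close to the stated range. For models of that size, 360 gives 360/27 = 13.3 and 360/30 = 12.0 people per parameter, both below 15.

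**5. What would close the gap by numbers alone.**
- At 40%: 400/0.40 = 1000 in total for the lower bound, and 600/0.40 = 1500 for the upper.
- With 900 kept: a deficit share of 400/900 = 44.4% for the lower bound, or 600/900 = 66.7% for the upper.

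**6. Sensitivity to the 40%.** If the Background range is taken as the range for this subgroup (an assumption, since the two definitions need not match), the subgroup is 900 × 0.30 = 270 to 900 × 0.50 = 450.

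**7. The other models.** The whole cohort of 900 exceeds 600. The complementary group has 900 − 360 = 540, which is above 400 though below 600.

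**The case against.** The strongest reply is that the benchmark is an optimum, the shortfall from 400 is only 10%, and the 40% is itself approximate. A share of 44.4%, within the range cited in the Background, would give 400. The text also refers to an SEM for the 360 without saying that it is the full Wilson-Cleary model. Table 1 has seven rubrics (five outcome levels, individual characteristics, and supports). With one latent variable for each, 7 × 3 = 21 parameters and 360/21 = 17.1 per parameter, inside the rule.

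Part of this stands. The rule is worded as an optimum, the gap to the lower bound is modest, and the 27 to 30 parameters are inferred. But the comparison of 360 with 400 to 600 needs no inference about model size, because both figures are printed. The seven-construct model is not in the text, and a question about whether the same structure differs points to the same model. The prevalence argument also runs the other way: at 30% the subgroup is 270.

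A reader might infer more than the document supports:

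- **That 900 is too small for the main SEM.** It is not, because 900 exceeds 600.
- **That 900 rests on this comparison alone.** The cohort also serves the trajectory analysis and is the sampling frame for the nested trials.
- **That loss to follow-up shrinks the subgroup further.** The sentence on longitudinal fitting can equally mean the whole-cohort model. With an assumed loss of 10 to 20%, the cohort would still number 810 to 720. Applying the same assumed loss to the 360 (324 to 288) presumes a longitudinal subgroup model that the text does not describe.
- **That the subgroup model is under-identified.** Identification depends on the structure of the model and its free parameters, not on the number of people. The subgroup is undersized against the plan's rule, which is a different matter.
- **That splitting on cognitive ability distorts the paths through range restriction.** This can happen, but the article does not say which measure or cut-point defines the group, or whether the fit is separate or joint. It is a secondary consideration for the full analysis plan.

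**Conclusion.** The Aim 1 text is inconsistent with itself on one point. It says the model needs 400 to 600 people, then supports the cohort size with a subgroup SEM of about 360, without noting that this is 10% below its lower bound and 40% below its upper. The conclusion rests on the article's 40% and on reading the subgroup model as the same Wilson-Cleary model, which the stated question implies. It does not depend on any assumed attrition or on an inferred parameter count.

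The consequence is limited. The multiplication is right, and neither the whole-cohort SEM nor the nested trials are affected. What needs correcting is the claim about what the lower-ability comparison can support.

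**What to change.** 1. State in the Aim 1 text that about 360 people support at most 18 free parameters at 20 per parameter, or 24 at 15 per parameter, under the plan's own rule.
2. State that a full-size SEM fitted separately to this subgroup is below the stated optimum and exploratory.
3. Preferably, test whether the structure differs by cognitive ability in one model fitted to all 900. One example is a two-group model with measurement parameters held equal across groups and a nested-model test of the structural paths. The group-specific parameters should be kept within the 18 to 24 that the smaller group supports. Other joint models could serve equally well, and that choice belongs to the analysts.

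The cost is a change of wording and of analysis specification. It needs no new data and no extra enrolment, whereas reaching 400 in the subgroup through enrolment alone would take 1000 people at 40%. The stated capability of the subgroup analysis becomes slightly less favourable.
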